## Abstract

Supplemental Digital Content is available in the text

## Introduction

1

In clinical practice, we often come across mesially inclined molars, whether due to an early loss of deciduous or permanent molars (from caries, periodontal disease, trauma), ectopic eruption, and second premolar anodontics, which results in an adjacent teeth impaction (second and third molars). In such cases it is common to find infraosseous defects in the mesial of the inclined molar and a reduction of the interradicular space in the distal region.^[1]^

One of the solutions for the prosthetic rehabilitation of this space would be the verticalization of these molars with opening or closing of the space or extraction in more severe cases, such as very severe angles or mobility of the element.^[1]^

However, this isolated vertical movement is very difficult to perform, especially with the most common clinical routine techniques, such as the use of springs and cantilevers,^[1]^ and is usually accompanied by an extrusion, which often produces premature contacts, and bite opening, interfering with the entire occlusion. A mechanical control with well-defined theoretical bases, with minimal undesirable effects, would be ideal.^[1]^

Verticalization of molars with skeletal anchorage consists of the dislocation movement of these teeth distally, without reactions in the most anterior segments of the arch.^[2]^ It is an interesting device because it is transitory, with skeletal anchorage (which does not allow the movement of the reaction unit) and fast results, with controlled forces.^[3]^ According to Roberts et al 1990^[4]^ and 1996,^[5]^ the skeletal anchorage movement rate of the second and third molars is approximately 0.5 mm / month, which corresponds to the linear rate of osteoclastic resorption.^[6]^

For the molar vertical movement, the mini-implants should preferably be installed distally to the disinclination direction, close to the occlusal plane, thus reducing the intrusive vector in the molar mesial and, consequently, its inclination.^[3]^ For lower molars, mini-implants should be placed in the retromandibular region.^[3]^ By placing a fixation attached to the molar, where possible (occlusal, distal, or mesial face), orthodontic activation can be performed through closed springs, tie wires or elastic bands.^[3]^

Nowadays, with the ease of access to orthodontic treatment, and with the new therapeutic possibilities, there has been an increase in adult demand for faster, more effective treatments with as few side effects as possible. These same adults are the ones who by 2010 had a toothless rate of about 7.4 teeth,^[7]^ requiring not only isolated orthodontic movement, but complete oral rehabilitation.

As an option, several studies have reported different methods for accelerating this orthodontic movement, which can be divided into 3 categories: biological, through local, or systemic drug administration (local injections of prostaglandins or administration of muscle relaxants); Mechanical or physical stimulus (vibratory forces, photobiomodulation, and laser); and surgical access to facilitate movement (corticotomies).^[8,9,10]^

The administration of systemic substances has been thought of in animal studies,^[11]^ as prostaglandin E2 and calcium gluconate, but human studies are still scarce and little explored, requiring further studies to assess their cost-effectiveness if they really affect dentoalveolar tissues and your safety. Local injections of drugs, vibration, or electrical stimulation, besides being able to cause pain and discomfort, would still require specific equipment and materials, just for this use, that is not so common in daily clinical practice. Added to this is the fact that the surgical treatment is an invasive procedure, with difficult acceptance by the patient.^[9]^

However, some care must still be taken. With excessive forces, there is a physiological decrease in the amount of tooth movement due to a decrease in vascularization in the compression areas, and an increase in bone density. In these cases, angiogenic stimulating effects of photobiomodualtion (PBM) may be beneficial for these patients.^[12,13,14]^

In this scenario, the use of PBM using laser or LED^[15]^ irradiation has been widespread, with good receptivity on the part of the patients, being easy to apply, painless, with minimal adverse effects and applied to different areas of dentistry.^[16–19]^

PBM has important analgesic, anti-inflammatory, biostimulatory, and tissue repair effects,^[20,21]^ that is, accelerating the processes of cell multiplication and regeneration, provided that the laser is used within the proper parameters.^[22]^ In pain, PBM acts on the production of betaendofirna (the body's natural pain reduction mediator),^[23]^ and inhibits the production of aracdonic acid^[24]^ (which, by generating metabolites such as prostaglandins and interleukins which bind to nociceptors, cause pain) and the number of nociceptive transmitters responsible for conducting nerve impulses.^[25]^

The modulatory action on tissues is the result of the ability of PBM to accelerate metabolic changes, increasing bone resorption and neoformation, essential for orthodontic movement to occur.^[26]^

In the inflammatory process generated by tooth movement, various cytokines, chemokines, and growth factors can be detected in crevicular gingival fluid (CGF).^[27]^ During orthodontic tooth movement, an increase in the expression of inflammatory mediators is expected,^[28,29]^ such as interleukins (IL). They are released by various cell types residing in the periodontal ligament, such as fibroblasts and osteoclasts, and these cytokines are responsible for bone remodeling and modulation of the inflammatory response. The most studied are IL-1β, IL-6, IL-8, IL-10, and TNF-α.^[30,31,32]^ Interleukin IL-1β is important because it stimulates osteoclastic activity and recruits leukocytes and other cellular mediators that contribute to the process of bone remodeling. Giannopoulos et al^.^^[33]^ and Yao et al^[34]^ observed an increase in IL-1β levels in relation to tooth movement. In turn, IL-6 is responsible for regulating local inflammatory immune responses and stimulating osteoclast formation and bone resorption activity.^[35]^ The presence of IL-8 stimulates osteoclast differentiation in orthodontically moved tooth compression zones.^[36]^ While TNF-α is considered a pro-inflammatory cytokine, and its increase stimulates osteoclastic activity to the detriment of an inhibition of osteoblast activity and apoptosis of osteocytes.^[37]^ Finally, IL-10 is considered an anti-inflammatory cytokine, and its presence indicates a late phase of inflammation. When found at elevated levels, there is a decrease in IL-1β, IL-6 and TNF-α release and osteoclastogenic activity.^[38]^ In order to evaluate cell dynamics, CGF sampling is a noninvasive and non-destructive method of choice.^[39]^

Given the importance of seeking balanced occlusion, it is necessary to correct the position of vertical molars in adult patients. Currently, mini-implants have enabled the correction of a dental element alone. Therefore it is very indicated in adults, however it is still necessary to accelerate the treatment time and modulate the inflammation bringing a less painful postoperative period with lower consumption of analgesics. In this sense, photobiomodulation has been used with good results in small orthodontic movements of adult patients such as molar intrusion. There was less pain and less production of inflammatory cytokines, indicating that PBM modulates the inflammatory response and accelerates movement. Although molar verticalization is a common movement among adult patients, so far no clinical studies have evaluated pain inflammation, movement rate, and quality of life of patients. Therefore, the present study aimed to evaluate the effects of PBM on orthodontic movement of vertical molars by evaluating the expression of proinflammatory cytokines, pain reduction, movement speed, and patients quality of life.

## Methods

2

This is a prospective, single-center, randomized, controlled, double-blind, 90-day follow-up trial that meets the criteria for a SPIRIT Statement clinical trial design. This protocol received approval from the Human Research Ethics Committee of *Universidade Nove de Julho* (certificate number: 3 533 219). Any complications or alterations will be reported and clarified to REC and reported in the publications. After verbal and written explanation of the study ([name]), patients who agree to participate in the study will sign the Informed Consent Form (ICF). If patients want to receive the research data, they can put the e-mail in the informed consent form and the full article can be checked as soon as it is published. The study will be conducted in accordance with the Helsinki Declaration (revised Fortaleza, 2013). The Project was registered at www.clinicaltrial.gov with NCT 04037709. The patients will come from [name]'s office and staff, located at [name]. There is no conflict of interest with regard to the clinics where the research will be conducted and with respect to any product used at work and with respect to any author involved in the study. Project receive grant from Brazilian National Coordination for the Improvement of Higher Education Personnel CAPES #690822 (CAPES Portuguese: Coordenação de Aperfeiçoamento de Pessoal de Nível Superior (CAPES).

The sample will consist of adult patients, who live in the city of São Paulo, Brazil, and who require lower molar verticalization for prosthetic rehabilitation. The description will be detailed in the item “Orthodontic verticalization mechanic and placement of the mini-implant”. The experimental design will consist of 2 groups (will be described in detail in the item “Experimental Design”). Samples will be collected for evaluation of inflammatory cytokines of crevicular gingival fluid. The intensity of pain will also be evaluated through the visual analog scale, the amount of medication taken and the vertical velocity of both groups. An OHIP-14 questionnaire will also be applied to measure oral health-related quality of life (Fig. 1  flowchart). Data will be published and there will be no restriction on including data for publication. All data will be available for consultation, and all patients will have access to their records at any time.

**Figure 1 F1:**
[figure not shown]
Flowchart.

**Figure 1 (Continued) F2:**
[figure not shown]
Flowchart.

### Sample size calculation

2.1

To achieve an effect size = 0.40 between 2 groups (Orthodontic verticalization mechanic and Orthodontic verticalization mechanic + PBM), to increase the molar verticalization velocity assuming the type 1 error of 0.2^[40]^ and 95% confidence level, the total sample size will be 34 patients, divided into 2 groups. The sample calculation was performed in Excel, based on the calculation formula described by Kadam and Bhalerao. Considering a 20% drop-out, 3 extra patients will be inserted into each group if there is dropout.^[41]^

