### Randomization

2.5

To randomly assign participants to the experimental groups, a 40-number draw (34 patients + 20% of drop out, if need be) will be conducted using the Microsoft Excel 2017 version program. The distribution of the groups will be identical (1: 1) for both groups. Distribution will be performed in a blocked manner (5 groups of 8 patients). Opaque envelopes will be identified with sequential numbers (1 to 40) and inside there will be information from the corresponding experimental group according to the order obtained in the draw. The envelopes will be sealed and remain sealed in numerical order until the time of mini-implant placement and laser application. The draw and preparation of the envelopes will be performed by a person not involved in the study. Immediately before the laser application, the treating researcher will open 1 envelope (without changing the number sequence) and perform the indicated procedure. Three additional patients will be included in each group due to the drop out predicted in every clinical study (considering a 20% drop out). The author of the research will be responsible for the storage (digital platforms) and tabulation of information, being the statistician responsible for analyzing the data obtained at the end of the research. These same envelopes will contain the patient records (with anamnesis sheet, ICF and radiographs) and will be kept on file.

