### Statistical analysis

2.14

Statistical analysis will be performed using only data obtained from patients who complete the study. The Kolmogorov-Smirnov test will be applied prior to data analysis to assess the normality of each parameter. Bidirectional analysis of variance (ANOVA) followed by Bonferroni test will be used to compare all measurements. All tests will be performed using Graphpad Prism 5 (GraphPad Software, San Diego, USA). The significance level will be set at p < 0.05.

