## Discussion

3

The study was characterized as a randomized, double-blind, placebo-controlled trial to minimize measurement bias (also referred to as information, observation or measurement), which is the result of systematic differences in the way data about the event of interest is obtained from the various groups under study.^[50]^

Randomization should be performed in prospective studies comparing the effect of an intervention (prophylactic or therapeutic) with their respective controls. The researcher distributes the intervention at random through randomization; Thus, the experimental and control groups are formed by a random decision process.^[50]^

The term double-blind refers to those trials in which neither the patient nor those responsible for their care and evaluation know what treatment he is receiving. Blinding will be performed by randomization during delivery of envelopes, and the group to which the patient belongs is confidentially informed on the brown envelope. The main reason for introducing a placebo-controlled group is to make patients’ attitudes as similar as possible to those of the treated group.^[50]^

For our study, the calculated sample was based on the “amount of motion x time” variable, following the Kadam, 2010,^[41]^ sample size calculation formula: N = 2 (ZA - Z1-β) 2σ2 / Δ2 reaching a “n” of 34 patients (17 patients in each group), with 20% dropout, totaling 3 more individuals in each group. Research participant dropout is unlikely during treatment because it has the mini-implant installed. Therefore, we limited our study to a 90-day follow up.

Our approach was based on a problem that can be pointed as one of the most recurrent conditions in the population, which is the loss of the permanent lower first molar.^[51,52]^ Of various causes, this situation can result in mesial migration of the second molars,^[53,54]^ affecting even the anterior teeth, with opening of diastemas and midline deviations.^[53,55]^ In such cases it is still common to find infraosseous defects in the mesial of the inclined molar, accompanied by a gingival recession and a reduction of the interradicular space in the distal region.^[1]^

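### The sample size statement contradicts itself on the error rates, prints the z-values subtracted, and does not yield 34 for a standardised effect of 0.40

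*Protocol article*

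**What the plan says.** Section 2.1 (Sample size calculation) opens with "To achieve an effect size = 0.40 between 2 groups", names the velocity of molar verticalization as the target, continues "assuming the type 1 error of 0.2", and in the same sentence adds a "95% confidence level, the total sample size will be 34 patients, divided into 2 groups". It says the calculation was done in Excel from a published formula. Dropout is handled separately: "Considering a 20% drop-out, 3 extra patients will be inserted into each group if there is dropout".

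The Discussion says that "the calculated sample was based on the" amount of movement over time, which matches the primary variable in section 2.13. It prints the formula as "N = 2 (ZA - Z1-β) 2σ2 / Δ2" and reports 34 patients, 17 per group.

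Section 2.5 fixes the allocation: "The distribution of the groups will be identical (1: 1) for both groups". Section 2.14 fixes the test level: "The significance level will be set at p < 0.05".

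The article states no power, no sidedness, no SD and no unit for 0.40.

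**The concern.** The statement has two visible faults and a result that does not follow from its inputs.

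- **Error rates.** A 95% confidence level means a type 1 error of 0.05, so 0.2 cannot also be the type 1 error. The analysis section tests at 0.05 as well. Since no power is given, 0.2 is most plausibly the type 2 error (80% power) under the wrong name.
- **Formula.** Sizing a comparison of two means adds the quantile for alpha to the quantile for power. With both quantiles positive, a minus sign makes the required number fall as power rises, to zero at 97.5% power.
- **Result.** With the repaired error rates and 0.40 as a standardised difference, the answer is several times 34.

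This is the only quantitative justification for the size of the trial, and it concerns the primary variable. A reader would take the trial to be adequately powered for an effect of 0.40. If it is not, a non-significant result could be misread as evidence that photobiomodulation has no effect on movement.

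**Working it through.** **Inputs.** Effect size 0.40 (2.1). Alpha 0.05, from the 95% level (2.1) and the test threshold (2.14). Type 2 error 0.20, by reading the misnamed 0.2 in 2.1 that way. Allocation 1:1 (2.5) with 17 per arm (Discussion). Two-sided testing is my assumption. Quantiles: 1.960 for two-sided alpha 0.05 and 0.8416 for 80% power.

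**1. Attempt to reproduce 34 with the formula as printed.** With σ = 1 and Δ = 0.40:

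n per arm = 2 × (1.960 − 0.8416)² / 0.40² = 2 × 1.2508 / 0.16 = 15.6, so 16 per arm and 32 in total. This is close to 34 but not equal to it.

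**2. Formula with the z-values added.**

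n per arm = 2 × (1.960 + 0.8416)² / 0.16 = 2 × 7.849 / 0.16 = 98.1, so 99 per arm. The t-test calculation gives 99.1, so 100. The total is 198 to 200 before dropout.

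**3. Power of the planned size at a standardised 0.40.** Normal approximation: 0.40 × √(17/2) = 1.166, and Φ(1.166 − 1.960) = Φ(−0.794) = 21.4%. The t-test gives 20.5%. With 20 per arm the t-test power is 23.4%.

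**4. Other readings of the printed inputs.**

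| Reading | Needed per arm | Power at 17 per arm (t-test) |
|---|---|---|
| d = 0.40, two-sided 0.05, 80% power | 99 (t-test 100) | 20.5% |
| d = 0.40, one-sided 0.05, 80% power | 78 | 30.7% |
| d = 0.40, alpha literally 0.2, two-sided, 80% power | 57 | 45.6% |
| d = 0.40, alpha literally 0.2, one-sided, 80% power | 36 | 62.5% |
| 0.40 as ANOVA f (d = 0.80), two-sided 0.05, 80% power | 26 | 61.9% |

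Pairing alpha 0.2 with 95% power needs 108 per arm two-sided or 78 one-sided. None of these readings gives 17.

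**5. 0.40 as a raw difference.** Solve the formula with added z-values for σ at n = 17: σ² = 17 × 0.16 / (2 × 7.849) = 2.72 / 15.698 = 0.1733, so σ = 0.416. With that SD, 17 per arm follows. The article does not give it.

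**6. What 17 per arm detects, whatever 0.40 means.** Normal approximation: (1.960 + 0.8416) × √(2/17) = 0.96 SD. The t-test gives 0.99 SD. So 17 per arm has 80% power for a difference of about 1.0 SD.

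**The case against.** The strongest defence is that 0.40 is never called standardised. The printed formula carries σ² and Δ² separately, and section 2.1 attaches 0.40 to a velocity, which has units. If 0.40 is a raw difference and the SD is about 0.416, the correct formula gives exactly 17 per arm. This stands as a possibility. It does not rescue the statement, because neither the SD nor a unit is given and the number is called an effect size, which usually means standardised. It does mean that the 20% power is conditional.

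The minus sign can also be defended: it is valid if Z1-β denotes a negative tail point. The formula then equals the usual sum and needs 99 per arm at a standardised 0.40, so this does not lead to 17 either.

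A repeated-measures ANOVA with f = 0.40, two time points and a correlation of 0.3 gives a between-group total of 34. The article, however, names the two-means formula for its calculation and states no correlation.

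A reader might infer more than the article supports:

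- **That the power simply is 20%.** This holds only if 0.40 is Cohen's d.
- **That subtracting the z-values produced 34.** Literal subtraction gives 32. Reaching 17 per arm takes a further guess, such as entering 0.80 in place of its quantile (2 × 1.16² / 0.16 = 16.8), and nothing in the text indicates this.
- **That the mislabelled error rate caused the number.** Relabelling alone does not lead to 34. The near match in step 1 uses alpha 0.05 and 80% power.

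**Conclusion.** The sample size statement is wrong as written, and 34 cannot be reproduced from it. Two parts are certain: the stated type 1 error of 0.2 contradicts the 95% level and the 0.05 threshold, and 34 does not follow from a standardised 0.40. The formula's sign is wrong for positive quantiles and otherwise needs a definition.

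The size of the gap depends on what 0.40 means, with two-sided alpha 0.05 and 80% power assumed. As a standardised difference, the natural reading, the trial has about one sixth of the patients needed (34 against 198 to 200). As f it has 34 against 52. As a raw difference with an SD of about 0.416 there is no shortfall, but the target is then a difference of nearly one SD. How the sponsor arrived at 34 remains an inference and the conclusion does not depend on it.

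**What to change.** Correct section 2.1 and the Discussion, in this order:

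1. State a two-sided type 1 error of 0.05 and a type 2 error of 0.20 (80% power).
2. Correct the formula to n per arm = 2 (Zα/2 + Z1-β)² σ² / Δ².
3. State whether 0.40 is d, f or a raw difference, with its SD and units.
4. Recompute.
5. Replace the present claim with what 17 per arm delivers: 80% power for a difference of about 1.0 SD and, if 0.40 is d, about 20% power for that effect.
6. Report the primary effect with a 95% confidence interval, and state that a non-significant result will not be read as absence of effect.

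No extra patients and no design change are needed. The cost is some rewording and a less favourable statement of what the trial can detect.

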### Experimental design

2.10

Immediately before photobiomodulation (PBM) the responsible researcher will remove and open 1 envelope (without changing the numerical sequence of the other envelopes) and perform the indicated procedure. Thus, the 34 patients will be allocated to the experimental and control groups (considering a 20% drop out) as follows:

G1- Control group (n = 17) - Molar verticalization + laser simulation (placebo) - the treatment of molar verticalization adjacent to tooth loss will be performed with the use of mini-implants for skeletal anchorage (described in detail in the item “2.11 - Orthodontic verticalization mechanic and placement of the mini-implant”), followed by simulation of laser use, since it will be off, being applied at the same points and in the same period of the group that will be irradiated. To mimic the laser action the noise of the BIP will be recorded. Laser mimicking will occur immediately, 3 and 7 days after placement of the mini-implant, and the same sequence will be applied 30 and 60 days after force application (elastomeric ligature replacement), 5 points for buccal and 5 points for lingual. The analgesic pack will be delivered to the patient who will be advised to use only in case of pain. Visual analog scale (VAS), initial molar inclination (panoramic radiography), number of analgesics in the last 10 days, quality of life questionnaire (OHIP-14) and CGF collection will be assessed at baseline. Pain and use of rescue medication will be evaluated in all sessions. CGF collection will always be performed on the second day of laser application in the 3 months of research (totaling 3 collections, outside the baseline) and the questionnaire (OHIP) after 90 days. Another panoramic radiograph will be solicited before the removal of mini-implant (after 90 days).

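### Three extra patients per group cover 15% drop-out, not the stated 20%, and the protocol does not settle whether those six are always enrolled

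*Protocol article*

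**What the plan says.** The base figure is in section 2.1 (Sample size calculation): "the total sample size will be 34 patients, divided into 2 groups". The same section adds the allowance, with a condition: "Considering a 20% drop-out, 3 extra patients will be inserted into each group if there is dropout".

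Section 2.5 (Randomization) gives the allowance twice, in two senses. It is conditional in the description of the draw, "a 40-number draw (34 patients + 20% of drop out, if need be", and unconditional a few sentences later: "Three additional patients will be included in each group due to the drop out predicted in every clinical study". The allocation is 1:1, with the block structure given as "Distribution will be performed in a blocked manner (5 groups of 8 patients", and envelopes numbered 1 to 40 are opened in order.

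Section 2.10 (Experimental design) words it differently again: "Thus, the 34 patients will be allocated to the experimental and control groups (considering a 20% drop out". It lists the control group as 17, and the experimental group both as 17 and as 17 plus 3.

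The Discussion repeats the allowance on top of 17 per group: "with 20% dropout, totaling 3 more individuals in each group".

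Section 2.14 (Statistical analysis) restricts the analysis to patients who complete the study.

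**The concern.** There are two separate problems.

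The first is arithmetic. An allowance for a loss rate must be large enough that the target remains after that rate is applied to everyone enrolled. The target is therefore divided by the retained fraction. Adding the loss rate as a percentage of the target always gives too few, and here that sum was also rounded down. With a completers-only analysis, every patient lost comes straight off the analysed sample, so a target of 17 per group that the enrolment cannot deliver at the planned loss rate is a misstatement of the planned information.

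The second is that the number to be randomised is not fixed. Sections 2.1 and 2.5 make the extra patients depend on drop-out, section 2.5 also says they will be included, and section 2.10 can be read as putting the allowance inside the 34. A reader cannot tell whether recruitment ends at 34, at 40, or somewhere between according to who has dropped out. The final size should not depend on losses observed during the trial.

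**Working it through.** **Inputs**
- Evaluable target: 34, or 17 per group (section 2.1; Discussion).
- Stated loss: 20% (sections 2.1, 2.5, 2.10; Discussion).
- Allowance: 3 per group, so 17 + 3 = 20 per group and 40 in all (sections 2.1, 2.5, 2.10; Discussion).
- Allocation: 1:1, five blocks of 8, envelopes 1 to 40 in order (section 2.5).
- Analysis set: completers only (section 2.14).

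The 34 is taken as given here.

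**1. Reproducing the plan's 40.** Adding 20% of the target gives 17 × 0.20 = 3.4 per group. Rounded down, this is 3 per group and 40 in total. In total terms, 34 × 1.20 = 40.8. The plan's figure therefore comes from adding a percentage of the target, with the fraction dropped.

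**2. What 40 delivers at 20% loss.** 40 × (1 − 0.20) = 32 completers, or 20 × 0.80 = 16 per group. That is 2 short of 34.

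**3. What loss 40 covers.** 6/40 = 3/20 = 15%.

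**4. What 20% loss requires.** n / (1 − 0.20): 34/0.80 = 42.5, so 43 in total. With equal groups, 17/0.80 = 21.25, so 22 per group and 44 in total. The extra needed is 5 per group, not 3.

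**5. Chance of reaching the target.** Assume that each patient is lost independently with probability 0.20. The number of completers among 40 is then binomial with retention 0.80, and the probability of at least 34 is 0.29. With 44 enrolled it is 0.75.

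**6. Effect on sensitivity.** Section 2.1 names no power; it labels 0.2 a type 1 error alongside a 95% confidence level. Assume 80% power, two-sided alpha 0.05 and a two-sample t test. The smallest detectable standardised difference is 0.991 SD at 17 per group and 1.024 SD at 16 per group. Put the other way, under a normal approximation in which 17 per group gives 80% power (a difference of 0.96 SD), 16 per group gives 77.6%.

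**7. Fit with the envelopes.** Five blocks of 8 make 40, with 4 per group in each block, so 20 per group, which is 17 + 3. Using every envelope fits exactly. Four full blocks end at envelope 32, so stopping at 34 falls at the second place of block 5. The two envelopes used from that block split one to each group with probability (4 × 4)/C(8,2) = 16/28 = 0.57; otherwise the groups stand at 18 and 16. In that case the six envelopes left are not three per group.

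**The case against.** The strongest objection is that this matters little. The shortfall is one patient per group and sensitivity barely moves. The Discussion also expects few losses because the mini-implant is in place. The base figure has a larger difficulty of its own: with the usual formula, a standardised difference of 0.40 at two-sided alpha 0.05 and 80% power (assumed) needs 99 per group. All of this stands as a statement about size. It does not make the 20% claim correct. Nor are losses remote, since section 2.4 automatically excludes anyone who cannot attend any of the 10 scheduled dates.

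Three stronger readings are tempting and are not supported.

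- A reader might infer that the extra patients cannot be fitted into the blocked envelopes, or that a replacement is steered to the group that lost a patient. No section says so. All 40 numbers are to be drawn beforehand in complete blocks and opened in sequence, and three more in each group is what using all of them produces. The difficulty arises only if the conditional wording is followed and recruitment pauses at 34.
- A reader might take section 2.10 to mean that 34 already contains the allowance, which would leave 34 × 0.8 = 27.2, about 27 completers. That is strained. Sections 2.1 and 2.5, the experimental-group entry in 2.10 and the Discussion all put the allowance on top of 34. The sentence is loose wording to be corrected.
- A reader might treat a possible 18:16 split as a defect. It has the precision of 2 × 18 × 16/34 = 16.9 per group, against 17.

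**Conclusion.** The point holds in limited form. The stated 20% is wrong for the stated numbers: 40 randomised covers 15% loss, and 20% loss leaves 32 evaluable rather than 34. This follows from the protocol's own figures without any assumption. The contradiction between conditional and unconditional enrolment of the six extra patients is also in the text, within section 2.5 itself and between it and section 2.1.

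The practical effect is minor: about one patient per group, and a detectable difference of 1.02 SD in place of 0.99 SD. Those two values rest on an assumed 80% power and two-sided alpha of 0.05. The allocation scheme itself is sound if all 40 envelopes are used. The correction is worth making because it is cheap and because it fixes the enrolment number before any losses are seen.

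**What to change.** 1. State one enrolment number: all 40 are randomised in envelope order, whatever drop-out is observed, with no replacement by group. Remove the conditional phrases from sections 2.1 and 2.5.
2. Use the same terms in sections 2.1, 2.5, 2.10 and the Discussion: 34 is the evaluable target (17 per group) and 40 is the number randomised (20 per group). In section 2.10, reword the sentence that attaches drop-out to the 34, and give both groups as 20 randomised.
3. Correct the rate. Either say that 40 allows for 15% loss, or keep 20% and say that it leaves 32 evaluable (16 per group), with the power for that number.
4. If 17 per group after 20% loss is really wanted, 22 per group (44) are needed. Since 44 is not a multiple of 8, the block structure would then have to be revised as well.

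Items 1 to 3 cost only wording, plus at most the six patients for whom the 40-number draw already provides. Item 4 would cost four more patients than planned.
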